#### Sample size

The statistical approaches chosen to measure outcomes takes into account the potentially clustered nature of the data collected.

The marginal effect of reablement versus home care as usual in a previous prospective longitudinal study was 0.107 [11]. This was taken as comparable to Cohen’s f^2^ [31] and indicative of a small to medium effect size. It was assumed that differences in effect size between different types are likely to be smaller than those seen between reablement versus usual care and have, therefore, used the relatively small effect size of f^2^ = 0.06. Using a sample size calculation for hierarchical multiple regression, without clustering, the minimum total sample size required to detect an effect size of 0.06 with a power of 80 % and an alpha of 0.05, and with up to twenty individual predictors and four reablement service type predictors would be 222.

In order to account for clustering in the sample size calculations, two reported estimates of intra-class correlations (ICC) and the associated design effects have been used [32]: i) a reported ICC of 0.007 for overall health with an average cluster sample size of 200; this would result in a design effect of 2.393; and ii) the highest reported ICC of 0.01355 in the study [32]. This was deemed necessary for the sample size estimate as people eligible for reablement are likely, as a group, to display less variation in overall health (and therefore a higher ICC). The ICC of 0.01355 was rounded to 0.014 and, using an average cluster size as above, results in a design effect of 3.786.

Inflated by the two design effects given above (2.393 and 3.786), the study will need to achieve a sample size of between 532 and 841. Assuming an attrition rate of 25 % between T_0_ and T_2_, the study will need to recruit between 710 and 1121 people in total. A pragmatic decision was made to recruit between these two figures, giving a sample of 800 people in total, around 200 per each of the four reablement service types to be evaluated in WP2.

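### The 800 to be recruited do not deliver the stated 80% power at the higher ICC the protocol calls necessary, and power at 800 is never restated

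*Protocol article*

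**What the plan says.** All of this is in the protocol article, Methods – WP2a, Sample size.

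- **Target effect.** The authors "used the relatively small effect size of f^2^ = 0.06" for differences between service types.
- **Unclustered size.** The calculation is for hierarchical multiple regression "to detect an effect size of 0.06 with a power of 80 % and an alpha of 0.05", and the total "with up to twenty individual predictors and four reablement service type predictors would be 222".
- **Lower ICC.** The first scenario is "a reported ICC of 0.007 for overall health with an average cluster sample size of 200; this would result in a design effect of 2.393".
- **Higher ICC.** The second scenario takes the highest ICC reported in the same source. The reason given is: "This was deemed necessary for the sample size estimate as people eligible for reablement are likely, as a group, to display less variation". The variation meant is that of overall health, and the authors conclude that the ICC will be larger. Then: "The ICC of 0.01355 was rounded to 0.014 and, using an average cluster size as above, results in a design effect of 3.786".
- **Requirement.** The two design effects lead to 532 to 841 analysed and, with 25% attrition between T0 and T2, 710 to 1121 recruited.
- **Decision.** "A pragmatic decision was made to recruit between these two figures, giving a sample of 800 people in total", which is about 200 for each of the four types.

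No power is given for 800 recruited under either ICC.

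**The concern.** The section argues for a higher ICC in this population, computes what that ICC requires, and adopts a size that falls well short of it. The choice is disclosed, but its consequence for power is not. The target of 800 is 90 above the lower recruitment figure (800 − 710) and 321 below the upper one (1121 − 800). Placing it between the two can suggest adequacy under both, although it is adequate only under the lower.

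Comparing outcomes between service types is the purpose of WP2a, and the study is meant to inform commissioners. A reader who finds one power figure will apply it to the study that is run. If the upper ICC holds, the chance of detecting the target effect is lower than that reader believes.

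**Working it through.** **Inputs, all from the Sample size section.** f² = 0.06; alpha 0.05; 20 individual and 4 service type predictors (tested set u = 4, total k = 24); cluster size m = 200; ICC 0.007 or 0.014; attrition 25%; 800 recruited.

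**Step 1. Reproduce the plan's figures.**

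The test is the F test of the R² increment, with denominator degrees of freedom v = N − k − 1. Two noncentrality conventions are common:
- (a) λ = f²(u + v + 1): 80% power needs N = 224, and power at 222 is 79.6%.
- (b) λ = f²N: 80% power needs N = 205, and power at 222 is 83.7%.

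Convention (a) comes close to the stated 222. Both are carried forward.

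Design effect = 1 + (m − 1) × ICC:
- 1 + 199 × 0.007 = 2.393
- 1 + 199 × 0.014 = 3.786

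Analysed: 222 × 2.393 = 531.2 (stated 532); 222 × 3.786 = 840.5 (stated 841).

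Recruited: 532/0.75 = 709.3 (stated 710); 841/0.75 = 1121.3 (stated 1121).

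Everything agrees within rounding.

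**Step 2. Power at the adopted size.**

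Analysed: 800 × 0.75 = 600. Effective n = 600/design effect, put into the same F test. The first figure in each power cell uses convention (a), the second (b).

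| ICC | m | Design effect | Effective n | Power, 4 type predictors | Power, 3 type contrasts |
|---|---|---|---|---|---|
| 0.014 | 200 | 3.786 | 158.5 | 60.6%, 67.3% | 65.8%, 72.4% |
| 0.014 | 150 | 3.086 | 194.4 | 72.5%, 77.7% | 77.1%, 81.9% |
| 0.007 | 200 | 2.393 | 250.7 | 85.4%, 88.5% | 88.7%, 91.3% |

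In the first row, for example, λ is 0.06 × (158.5 − 20) = 8.31 under (a) and 0.06 × 158.5 = 9.51 under (b). The effective n is 158.5/222 = 71% of what the plan requires.

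The rows with m = 150 assume that the cluster size of 200 is the recruited number per type (800/4), so that 25% attrition reduces it to 150. The rows with three contrasts assume that the four types are coded against a reference (u = 3, k = 23).

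With the unrounded ICC of 0.01355 and m = 200, the design effect is 3.696, the effective n 162.3, and power 62.0% to 68.6% with four type predictors.

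**Step 3. The ICC at which 600 analysed just meets 222 effective.**

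Design effect allowed: 600/222 = 2.703.
- m = 200: (2.703 − 1)/199 = 0.0086
- m = 150: (2.703 − 1)/149 = 0.0114

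Both lie below 0.014.

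**Step 4. Effect detectable with 80% power at ICC 0.014, m = 200, four type predictors.**

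Solving the same F test for f² at effective n 158.5 gives 0.089 under (a) and 0.078 under (b), against the planned 0.06.

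**The case against.** **The compromise is in plain view.** The article prints 710 and 1121 and calls the choice between them pragmatic. The 80% is attached to the unclustered 222, and the article never says that 800 gives 80% at the higher ICC. This stands as far as it goes: no printed figure is false. But 80% is the only power given, it is carried through to the 532–841 range, and nothing tells the reader what 800 delivers.

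**The lowest figures pair 600 analysed with clusters of 200.** If 200 is the recruited number per type, clusters shrink with attrition, and four types allow only three free contrasts. This stands, and it is why the result must be given as a range. Yet 200 and four predictors are the plan's own inputs. Changing either one alone leaves power below 80% at ICC 0.014; changing both gives about 77–82%.

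**The multilevel analysis includes time.** Data from people lost before T2 may contribute, so 600 may be conservative by an amount the documents do not give. As a bound on the printed inputs, 800 with no loss at all gives 800/3.786 = 211.3 effective, still under 222, with power of about 77–82%.

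**Stronger readings are not supported.** A reader might infer that the authors judged 0.014 the more likely value or 0.007 too low. The text says only that this population probably has a higher ICC, and 0.014 may have been meant as an upper scenario. A reader might also infer that a non-significant comparison is to be taken as equivalence of types; the article proposes no such reading.

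**Conclusion.** The point holds as a mismatch between the stated power and the adopted size. At ICC 0.014, on the plan's printed inputs, 800 recruited and 600 analysed give about 61–67% power for f² = 0.06. The figure is about 72–78% with clusters of 150, and about 77–82% only with clusters of 150 and three contrasts together. At ICC 0.007 with clusters of 200, power is 85.4–88.5%, so the design is adequate under the lower scenario and is not invalid. These figures rest on the plan's f², alpha, ICCs and attrition, on a design effect applied to the sample size, and on analysis of completers at T2.

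It would go too far to call this a calculation error, since the printed figures all reproduce, or to conclude that 1121 must be recruited. The defect is that the section presents the higher ICC as needed for the estimate, sizes the study below it, and leaves the resulting power unstated.

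**What to change.** Keep 800 and add to the end of the Sample size section a statement of what it delivers, for example:

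*With 800 recruited and 600 analysed, power for f² = 0.06 is about 85–88% at ICC 0.007 and about 61–67% at ICC 0.014, assuming clusters of 200 and four service type predictors; the ranges reflect the noncentrality convention. With clusters of 150 after attrition, power at ICC 0.014 is about 72–78%, or about 77–82% if service type is coded as three contrasts. Power of 80% holds up to an ICC of about 0.0086 with clusters of 200, or 0.011 with clusters of 150 (four type predictors). At ICC 0.014 with clusters of 200, the f² detectable with 80% power is about 0.08–0.09.*

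The authors should first settle which cluster size and type coding the analysis will use, and then keep only the matching figures. The text should not describe either ICC as the more likely one unless the authors are prepared to justify that.

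The cost is a few sentences. No extra participants are needed; the stated power becomes less favourable under the upper ICC.

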#### Analysis

Baseline (T_0_) demographic and social characteristics of participants at each case site will be summarised using descriptive statistics. Categorical data will be reported as counts and percentages. Continuous data will be expressed as mean values with standard deviations, however median and inter quartile range will be reported if the data is skewed. Multilevel modelling has been chosen as the most appropriate analytical approach for this type of study design, which allows exploration of more than one explanatory variable at different levels and facilitates analysis of cross-level interactions [33]. This will allow separate analysis of the impact of service user characteristics, the types of reablement service, and time on service user outcomes, and identification of any possible interactions between them. This approach is thus ideally suited to exploring questions of effectiveness and which sub-groups of service users might benefit most.

### Process evaluation (WP2b)

A process evaluation, comprising interviews with reablement professionals, service users and carers, will develop an understanding of the immediate and wider context in which reablement models exist, the different effects reablement can have and how, and why, these effects vary between recipients and different services.

### Methods - WP2b

A mixed-methods [34] approach will be used for the process evaluation. Data collected in WP1 will be used alongside data from qualitative interviews with commissioners, practitioners, service users and carers. These semi-structured interviews will allow more in-depth exploration of local policy, structures and process arrangements, the components of the service, service costs, how these components interact and the effects of these interactions.

The interviewing process will take a staged approach. In order to understand local structures, systems and service delivery/practice issues interviews will be conducted with lead commissioners, service managers and practitioners. Interviews will be conducted with service users and carers to understand their experience of reablement and goal achievement (*n =* 10 to 12 per service type). Further interviews with reablement practitioners (*n =* 6 to 8 per service type) will also be conducted to identify the barriers and facilitators to achievement of service user outcomes.

#### Sampling and recruitment

##### Staff

The aim is to recruit the lead commissioner/s for reablement and the reablement service manager/s within each of the four service types as described in WP2a. Practitioners who deliver the reablement programmes to service users will also be interviewed; this includes interviews (with service users’ permission) with the reablement practitioner supporting service users recruited to the process evaluation. The number of practitioners interviewed will depend on the size and structure of the team (this will be unknown until case sites are confirmed following WP1 cluster analysis). However, recruitment from these groups of staff will be undertaken and the views of different professional groups and grades within the team will be gathered until data saturation is achieved.

##### Service users

The aim is to recruit 10–12 service users per service type. Service users will be identified from the outcomes evaluation sample when they are discharged from the reablement service. Half of the service user sample will be ‘return home’ (RH) clients and the other half will be ‘remain at home’ (RAH) clients. Purposive sampling will be undertaken within these two groups to include, for example, different levels of goal achievement and personal and socio-demographic factors that affect goal achievement (based on evidence from staff interviews and preliminary analysis of data collected at discharge, i.e. T_1_ outcomes data).

##### Carers

Interviews will be undertaken with up to ten carers in each case site. Initially carers of service users taking part in the process evaluation will be recruited, but we are aware that some service users might not have a carer. Therefore, carers of other recipients of reablement services will be recruited if needed. Carers will be over 18 years of age and able to give informed consent. Both carers supporting service users in the (RH) group and in the (RAH) group will be recruited.

#### Analysis

Data will be analysed within, and across, participant and reablement service types using the Framework approach to managing and thematically analysing qualitative data. The Framework approach facilitates systematic data management and allows audit trails of the data management process [35].

### Economic evaluation (WP2c)

The economic evaluation will use data collected in WP1 and WP2 to compare the costs and consequences of the four different generic reablement service types in comparable populations to indicate which offers the best value for money. It will comprise: a rapid systematic review [36]; a cost-effectiveness analysis from the perspective of the UK NHS; a cost-consequence analysis taking a societal perspective; the development of a decision analytic model and costing vignettes.

#### Outcomes

The cost-effectiveness analysis will consider health outcomes expressed in quality-adjusted life years (QALYs) using EQ-5D-5L collected during WP2a. The cost-consequence analysis will consider QALYs and social care-related quality of life, using the ASCOT SCT-4 collected during WP2a. Both EQ-5D-5L and ASCOT SCT-4 will be valued using the UK population tariffs [37, 38].

#### Resource use and costs

Resource use will be collected directly from study participants using a bespoke questionnaire, the Service and Care Pathway Questionnaire (SCPQ), collected at T_0_, T_1_ and T_2_. The SCPQ will collect data on the use of health, social care and voluntary services, both publicly funded and privately paid, and informal care. The SCPQ will be piloted with a sample of service users and amended as required prior to the commencement of data collection. Study participants will be asked for their use of hospital services over the previous 6 months. The recall period for other services will be subject to the results of the pilot.

Resource use will be valued with national costs whenever possible. For the services where national costs are not available, the process evaluation in WP2b will obtain the relevant local costs. The cost-effectiveness analysis will include the costs from the perspective of the UK NHS and publicly funded social care. The cost-consequence analysis will include costs falling on all sectors, namely UK NHS, publicly funded social care, voluntary services, private costs and informal care.

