#### Data collection

Service users recruited to the project will be the main source of data collection. Individual participant outcomes will be measured at three time points: within the first week of receiving the reablement service (T_0_); within a week of discharge from the reablement service (T_1_); and 6 months post-discharge (T_2_ = T_1_ + 6 months).

In addition, practitioners conducting reablement service assessments and reablement practitioners will be asked to collect background data on health, functioning and living situation. For each research participant, the reablement practitioner conducting the reablement service assessment (T_0_) will complete a study entry form and information about functional status, which includes questions on: health status; impairments (e.g. memory/confusion; cognitive impairment); living situation (e.g. living alone versus with partner/other family) and informal carer involvement. Services will also be asked to provide the study with routinely collected service delivery/audit data.

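### The single 6-month hospital recall does not fit T1: it overlaps the T0 recall, so hospital use during reablement cannot be separated unless admissions are dated

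*Protocol article*

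**What the plan says.** Under Resource use and costs (WP2c), resource use comes from participants through "the Service and Care Pathway Questionnaire (SCPQ), collected at T_0_, T_1_ and T_2". The hospital item has one stated recall period, with no distinction between time points: "Study participants will be asked for their use of hospital services over the previous 6 months". The next sentence leaves only the remaining items open: "The recall period for other services will be subject to the results of the pilot". The same paragraph allows for revision: "The SCPQ will be piloted with a sample of service users and amended as required prior to the commencement of data collection".

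The time points are defined under Data collection (WP2a). T0 falls "within the first week of receiving the reablement service (T_0", T1 falls "within a week of discharge from the reablement service (T_1", and the last is "6 months post-discharge (T_2_ = T_1_ + 6 months". The interval from T0 to T1 is therefore about the length of the reablement episode. The article describes that episode as time-limited and gives no number of weeks.

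Service level outcomes separates return-home users, who come from hospital or residential care after an acute episode, from remain-at-home users. The article does not say how SCPQ answers are assigned to intervals or whether admissions are dated.

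**The concern.** One recall length is applied to three questionnaires that are not equally spaced. At T2 the window coincides with the interval since the previous questionnaire. At T0 it is a history. At T1 it covers the reablement episode plus a stretch of pre-service time that participants have already reported on.

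That stretch is where the index stay of a return-home user referred from hospital is likely to lie. The service cannot have influenced such a stay, and it may be expensive compared with hospital use during reablement. Remain-at-home users need have no such stay. The service types are not randomised, and WP1 plans a separate cluster analysis on case mix and eligibility, so the mix of users may differ between types. Hospital costs feed the cost-effectiveness and cost-consequence analyses, which are meant to show which service type is the best value.

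**Working it through.** The plan states no figure on this point to reproduce, so the check is window arithmetic.

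**Inputs.** Recall is 6 months, taken as 26 weeks (Resource use and costs). T0 is in the first week of the service, T1 is within a week of discharge, and T2 is T1 + 26 weeks (Data collection). Let *d* be the number of weeks from T0 to T1. The documents do not give *d*, so a range is assumed.

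**Step 1: which calendar time each answer covers**, with T0 as week 0.
- T0 answer: week −26 to week 0.
- T1 answer: week *d* − 26 to week *d*.
- T2 answer: week *d* to week *d* + 26.

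The T2 window meets the T1 time point exactly. For *d* < 26, the T1 window contains 26 − *d* weeks before T0, all of them also inside the T0 window.

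**Step 2: share of the T1 window that precedes T0**, (26 − *d*)/26.

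| Assumed *d* (weeks) | Weeks before T0 | Share |
|---|---|---|
| 2 | 24 | 92% |
| 4 | 22 | 85% |
| 6 | 20 | 77% |
| 8 | 18 | 69% |
| 12 | 14 | 54% |
| 16 | 10 | 38% |
| 26 | 0 | 0% |

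A one-week shift in *d*, as the visit tolerances allow, moves each share by 1/26, about 4 percentage points.

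**Step 3: summing the answers.** Three recalls make 3 × 26 = 78 weeks. The distinct time covered is 26 + *d* + 26. At *d* = 6 that is 58 weeks, so 78 − 58 = 20 weeks are asked about twice.

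**Step 4: subtracting the answers.** Write U(a, b) for hospital use between weeks a and b.

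T1 − T0 = [U(*d* − 26, 0) + U(0, *d*)] − [U(−26, *d* − 26) + U(*d* − 26, 0)] = U(0, *d*) − U(−26, *d* − 26).

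The shared stretch cancels, but use in the earliest *d* weeks of the T0 window is taken off as well. The result falls short of use during reablement by that amount and can be negative. Undated answers therefore do not isolate U(0, *d*).

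**Step 5: the comparison between types.** If each hospital-referred return-home user had one index stay that was reported at T1 and charged to T0–T1, without adjustment, the spurious difference between two types would be the difference in their shares of such users, in stays per user. The documents give no shares, so no figure follows.

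**The case against.** A reader might infer that index admissions will be charged to the reablement period. The documents do not say so. No passage uses the T1 answer as the cost of T0–T1, sums the T0 and T1 answers, or says that admissions are undated. An article may reasonably leave the allocation of costs to intervals to a fuller document, and admission dates on the form would separate the periods. This part of the objection stands, and it limits the point to a risk created by the stated window.

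The recall sentence also does not name T1, and the questionnaire is not shown, so three time-specific wordings may have been condensed into one. That lowers confidence. Against it, the sentence follows directly on a form collected at all three time points, and only the other services' recall is expressly left to the pilot.

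It is likewise tempting to say that the index stay of every hospital-referred return-home user falls in both windows. That depends on the length of reablement and the timing of the stay, neither of which is given. Bias between types is also not established: the economic evaluation refers to comparable populations, and adjusting for referral route would reduce any such bias.

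The suggestion that the T0 answer alone could separate the periods does not stand, as Step 4 shows.

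**Conclusion.** The point holds as a mismatch in a stated data-collection rule. Read as written, the 6-month hospital recall suits T0 and T2 but not T1, unless reablement lasts about six months. At assumed lengths of 2, 6 and 12 weeks, 92%, 77% and 54% of the T1 window precedes T0, and even at 16 weeks it is 38%. The mismatch does not depend on one assumed duration, but its size does.

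The consequence is conditional. If admissions are not dated, hospital use during reablement cannot be recovered from the questionnaires, and costs could be double counted or misattributed. If, in addition, the return-home share differs by service type and is not adjusted for, the cost comparison could be biased. The documents establish neither condition. The issue is confined to hospital resource use at T1; the primary outcome, EQ-5D-5L, and the QALYs are untouched. It should be corrected, because periods merged at collection cannot be separated afterwards from undated answers.

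**What to change.** At T1, ask about hospital use since reablement started, with the person's start date printed on the form. Alternatively, collect admission and discharge dates and state that stays before the service are excluded from T0–T1 costs. T0 may fall up to a week after the start of the service, so say which questionnaire counts those first days. Keep 6 months at T0, as a baseline covariate, and at T2.

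The cost is one wording change to the SCPQ, made at the pilot stage that the article places before data collection. Dates ask a little more of participants but leave the allocation rule open to later checking. If the form is already dated or anchored at T1, a sentence saying so settles the point.
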